### Interventions

#### Surgical treatment

Different surgical opportunities and techniques for cervical fixation exist. The choice of technique depends on the severity of the cervical spine involvement and the surgeon's preference. Surgery will be performed according to local standards and to the discretion of the surgeons, but a standardized minimal surgical technique is required. All approved cervical spine fixation systems are allowed in this trial. If AAS is present a C1–C2 screw fixation according to Magerl or Harms with or without wiring techniques, or a Hook C1–C2 fixation will be performed. When VT has occured, the cranium will be fixated to the upper cervical spine with fixation to the C1–C2 screws. For each patient, the surgeons will register which technique they have used.

#### Conservative treatment

Conservative treatment consists of antirheumatoid drugs (i.e, NSAID, DMARD, biologicals). The choice of drugs is to the discretion of the rheumatologist. Occurrence of progressive neurological deficits, progressive radiological abnormalities, and intolerable pain represent a failure of conservative management and are an indication for surgical fixation.

#### Cohort study

Many patients with rheumatoid arthritis do have cervical spine involvement but only a small proportion of these patients will be eligible for randomization. All patients with RA and AAS excluded for the randomization group will be offered to be followed in a separate cohort study design. The inclusion and exclusion criteria are only important for the group of patients that will be randomized and not for patients in the cohort group. Criteria for the cohort group are shown in table 4. Patients with an AADI less than 5 mm will be treated conservatively until the AADI enlarges. Patients with an AADI larger than 12 mm will be offered surgery. A follow up with X-rays and MRI scans of the cervical spine will be performed at predefined time intervals. The neurological and radiological outcome and quality of life will be analyzed.

### Primary and secondary outcome parameters

***The primary outcome ***is the occurrence of an event. Events are defined as 1) neurological deficit, 2) radiological progression, 3) surgery, 4) resurgery, 5) death. (see table 5).

1). Neurological deficit is defined as a worsening in the Ranawat scale to IIIA or IIIB, or a deterioration of the MDI score >3 points. The Ranawat classification is a neurological classification and useful in evaluating patients, planning treatment and evaluating results. Class I patients have no neurological deficit, Class II patients have subjective weakness with hyperreflexia and dysesthesia. Class IIIA patients have objective weakness and long tract signs. Class IIIB patients are wheelchair bound or bedridden. The Ranawat classification fails to differentiate reliably between classes II and IIIA, the area of most clinical interest to the operating surgeon [45]. Casey and Crockard developed and validated the MDI according to the Stanford HAQ. The MDI consists of 10 functional questions. The more severe a patient has been disabled the higher the score [45].

2). Radiological progression is defined as an enlarged AADI of more than 12 mm, development of VT with impingement of the spinal cord or medulla oblongata, or signs of myelopathy. The Redlund Johnell method will be used to measure the severity of VT, which is the distance of the base of C2 to the palato-occipital line of McGregor (less than 34 mm in men and 29 mm in women) [11].

3). Incidence of surgery in the conservative treatment group. One of the goals of the conservative treatment is to avoid surgery for intolerable pain for example. The surgical rate is therefore an indication of the success or failure of the conservative treatment policy.

4). The incidence of resurgery at the cervical spine in the early surgery group will be an indication of the failure rate for surgery.

5). Death: all causes.

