**Design:**

In this international multicenter randomized clinical trial, early surgical atlantoaxial fixation in patients with rheumatoid arthritis and radiological abnormalities without neurological deficits will be compared with prolonged conservative treatment. The main research question is whether early surgery can prevent radiological and neurological progression. A cost-effectivity analysis will be performed. 250 patients are needed to answer the research question.

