### Sample size/power calculation

The sample size is calculated on the basis of the outcome difference during the follow-up period of at least 5 years. Hypothetically, 8% of included patients will worsen in the 5 year follow up period resulting in an event (Kaplan Meier) (16,21). In the early surgery group the event rate is expected to be 2% or less [44]. 2% is chosen because it has to be a save alternative to 'wait and see'. A two-sided log rank test with an overall sample size of 250 patients, achieves 90% power at a 0.05 significance level to detect a difference in groups 1 and 2 after 5 years of follow up. Patients enter the study during an accrual period of 2 years. 50% of the enrolment is complete when 50% of the accrual time has past. A follow-up period of 5 years with a 20% loss from group 1 and a 20% loss from group 2 is calculated.

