### Cost-effectiveness and cost-utility analysis

The aim of the economic evaluation will be to determine and compare the total costs for patients receiving surgery or conservative care, and to relate these costs to the effects of the interventions. The economic evaluation will be conducted from societal perspective and will be carried out according to the intention-to-treat principle. Bootstrapping will be used for pair-wise comparison of the mean differences in total costs between the intervention groups. Confidence intervals will be obtained by bias corrected and accelerated (Bca) bootstrapping using 2000 replications.

Cost-effectiveness ratios will be calculated by dividing the difference in mean costs of the two interventions by the difference in mean effects of the two interventions. Ratios will include the primary clinical effect measures of the trial. Cost-utility ratios will also be calculated. Ratios will be graphically presented on cost-effectiveness and cost-utility planes. Acceptability curves will also be presented.

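### The primary composite counts a first operation as an event in the conservative arm only, so a significant result would not by itself show that early surgery prevents neurological or radiological progression

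*Protocol article*

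**What the plan says.** In *Primary and secondary outcome parameters* the Protocol article makes the primary outcome the occurrence of an event: "Events are defined as 1) neurological deficit, 2) radiological progression, 3) surgery, 4) resurgery, 5) death". The numbered explanations then make two of the five components specific to one arm:

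- Component 3 is "Incidence of surgery in the conservative treatment group". The reason given is that "One of the goals of the conservative treatment is to avoid surgery for intolerable pain for example", so the surgical rate is read as success or failure of the conservative policy.
- Component 4: "The incidence of resurgery at the cervical spine in the early surgery group will be an indication of the failure rate for surgery".

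The allocated first operation in the early-surgery arm is not an event. *Statistical analysis* makes the composite the primary outcome at the 5-year and 10-year analyses, under intention to treat.

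The triggers for surgery in the conservative arm are in *Conservative treatment*: "Occurrence of progressive neurological deficits, progressive radiological abnormalities, and intolerable pain represent a failure of conservative management and are an indication for surgical fixation". No threshold is attached to the radiological trigger. Radiological progression as an event does have criteria: AADI above 12 mm, vertical translocation with impingement, or signs of myelopathy.

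The abstract states: "The main research question is whether early surgery can prevent radiological and neurological progression". Question 1 in *Main research questions* likewise asks about progression of subluxation and vertical translocation, with or without complaints and neurological disability. For the economics, *Cost-effectiveness and cost-utility analysis* says "Ratios will include the primary clinical effect measures of the trial", and *Economic evaluation* also costs surgery in the conservative group.

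**The concern.** The same procedure is the assigned treatment in one arm and a failure in the other. A conservative patient operated on for intolerable pain, with no deficit and no radiological progression as defined, has a primary event. A patient in the same state in the early-surgery arm does not.

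That component also depends on judgement. Pain and an unquantified radiological change are assessed by clinicians who necessarily know the allocation, and the threshold for operating feeds directly into one arm's event count.

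At stake is what the primary result means. A significant composite could reflect deferred operations alone and still be reported as evidence that early surgery prevents progression, which is the question the article poses. The cost-effectiveness ratio would carry the same ambiguity if the composite is its effect measure.

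**Working it through.** **Inputs from the article** (*Sample size/power calculation*): 250 patients, two-sided log-rank test at 0.05, events 8% against 2% at 5 years, 2-year uniform accrual, 5 years of follow-up, 20% loss per arm.

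**Assumptions:** 1:1 allocation (125 per arm), exponential event times, and all surgery and resurgery rates. The article states none of these.

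**1. The plan's own figure.** The hazard ratio is ln(0.98)/ln(0.92) = 0.242. Schoenfeld's formula for 90% power gives 4(1.960 + 1.282)²/(ln 0.242)² ≈ 21 events. The stated design yields about 13, and power Φ(√13.1 × 1.418/2 − 1.960) ≈ 73% (about 60% by Freedman's formula). The stated 90% is not reproduced. That is a separate matter, and the present point does not depend on it. The planned difference is (0.08 − 0.02) × 125 = 7.5 patients, so few operations are needed to match it.

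**2. Composite when progression is identical.** Let s be the 5-year rate of shared events (deficit, radiological progression, death) in both arms, x the added surgery in the conservative arm and r the resurgery in the early arm.

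- Conservative arm: 1 − (1 − s)(1 − x). With s = 2% and x = 5%, 8%, 10%, this is 6.9%, 9.8%, 11.8%.
- Early arm: 1 − (1 − s)(1 − r). With s = 2% and r = 0, 2%, 5%, this is 2.0%, 4.0%, 6.9%.

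**3. Simulated log-rank test.** Each rate p becomes a hazard −ln(1 − p)/5, loss included. Probability of a significant result favouring early surgery, with no difference in shared events:

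| Shared events | Resurgery | Surgery 5% | Surgery 8% | Surgery 10% |
|---|---|---|---|---|
| 2% | 0 | about 50% | about 80% | about 92% |
| 2% | 2% | about 17% | about 47% | about 67% |
| 2% | 5% | about 2% | about 13% | about 27% |
| 8% | 0 | about 23% | about 46% | about 62% |

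With neither surgery nor resurgery added, the figure is 2–3%, the expected half of a two-sided 5%.

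**4. Staying within the planned 8%.** With s = 2% and the conservative composite fixed at 8%, x = 1 − 0.92/0.98 = 6.1%. With no resurgery the probability is about 62%.

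**5. Check by counts.** With 3 shared events per arm and no resurgery, 7 extra operations give 10 against 3. The pooled rate is 13/250 = 0.052, the standard error √(0.052 × 0.948 × 2/125) = 0.0281, and z = 0.056/0.0281 = 1.99 (Fisher's exact p = 0.08). With 3 resurgeries in the early arm, 12 extra operations are needed to pass z = 1.96.

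**The case against.** The composite has a stated rationale. Surgery marks failure of the conservative policy and resurgery marks failure of the surgical one. For a comparison of two strategies that is defensible, and *Conservative treatment* is consistent with it. Later surgery may also forestall progression that would otherwise have counted, so ignoring it is not neutral either. This stands as a reason to keep the composite. It does not turn the composite into an answer about progression.

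Resurgery is a counterweight. When it is about as common as conservative-arm surgery, the advantage disappears, and it could reverse. This stands, and it is why the range above is wide. The article plans the whole early-surgery composite at 2% or less, which leaves little room for frequent resurgery, but that is a planning assumption. A second operation is also not equivalent to a first.

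Some protection is already planned: imaging findings as a secondary outcome, MDI and Ranawat at the 2-year analysis, exploratory comparisons by surgery actually received, and QALY-based cost-utility. None of these is named as the analysis that decides a claim about progression at 5 years.

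Some stronger readings are tempting but unsupported:

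- A reader might treat 92% as a false-positive rate against a nominal 5%. At 11.8% against 2.0% the composite as defined truly differs, so 92% is power.
- A reader might infer that operations could be done on preference, or well below 12 mm. The article lists three triggers, preference is not among them, and it gives no radiological threshold.
- A reader might tie the differing equipoise between sites to later surgery. The text applies it to eligibility and randomisation intervals.
- A reader might call the economics double counting against one arm. Resurgery is likewise both an effect and a cost, and the ratios are not confined to the composite.

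**Conclusion.** The point holds as a problem of interpretation. The composite can reach significance in favour of early surgery with identical neurological and radiological progression, so it cannot alone answer the question in the abstract and in *Main research questions*.

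The size depends on rates the article does not give. Over the grid in the table, the probability runs from about 2% (5% surgery, 5% resurgery) to about 92% (10% surgery, no resurgery), and is about 62% if the conservative composite stays at its planned 8% with no resurgery. The upper figure is the most favourable case for the concern and should not be quoted alone.

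The article refers to a Table 5 for the event definitions, which was not available. Any further restriction there would need checking.

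**What to change.** Keep the composite, described as a measure of strategy failure, and make these changes:

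1. Pre-specify a symmetric key analysis of neurological deficit, radiological progression (as already defined) or death. Show neurological deficit or death alone beside it.
2. Ascertain these events in every randomised patient to 5 years, regardless of later surgery, and use the same Kaplan-Meier and log-rank methods.
3. State that any claim that early surgery prevents neurological or radiological progression must rest on this analysis.
4. Report surgery and resurgery separately by arm.
5. Use the symmetric endpoint as the clinical effect in the cost-effectiveness ratio, beside the planned QALY analysis, since conservative-arm surgery already enters as a cost.

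No clinical rule changes and no new data are needed, since *Follow up* already schedules clinical and radiological assessment to 10 years. The real cost is power. If deficit or death occurred in 4% against 1% (assumed rates), 250 patients would give about 33% power; at 5% against 2%, about 25%. The symmetric analysis should therefore be presented as an estimate with its confidence interval, and the stated 90% power should not be attached to it.

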#### Secondary outcome parameters

1) 'Perceived recovery/deterioration.' This is a seven-point Likert scale measuring the perceived recovery or progression, varying from 'completely recovered' to 'worse than ever'.

2). The American Spinal Injury Association (ASIA) and International Medical Society of Paraplegia have developed a standard form for capturing clinical information when evaluating a patient who has had a spinal cord injury. The ASIA score is a motor and sensory quantifying score of both arms and legs [46]. The ASIA score will be used once neurological deficits have occurred.

3). The Disease Activity Score (DAS-28) is a classification used by many rheumatologists and is a measure of the overall disease activity of RA. In Europe the DAS is the recognized standard in research and clinical practice. For a good comparison of the severity and disability due to the RA inflammatory process between all patients in the two treatment groups of the different countries the DAS-28 will be used. The following parameters are included in the calculation: Number of joints tender to touch (TEN), Number of swollen joints (SW), Erythrocyte sedimentation rate (ESR), patient assessment of disease activity [47].

4). VAS pain will be measured of pain in the neck and occiput before randomization and during the follow up. Pain will be assessed on a horizontal 100 mm scale varying from 0 mm, 'no pain', to 100 mm, 'the worst pain ever' [48].

5) EuroQol classification system and VAS rating personal health [49]. A cost-utility analysis will be performed using QALY's based on the EuroQol questionnaire, which has been validated in many studies and is easy to fill out. Patients describe their general health status using the EuroQol classification system, consisting of 5 questions on mobility, self care, usual activities, pain/discomfort, and anxiety/depression. Patients also rate their personal health using a visual analogue scale (VAS) ranging from worst imaginable health to best imaginable health.

6) Short-Form 36 (SF-36). Quality of life will also be assessed using the RAND-36 questionnaire [50]. This is a generic health status questionnaire, which can easily be filled out at home. The questionnaire consists of 36 items on physical and social functioning.

7) Imaging findings. The results of the differences between the baseline X-ray, MRI and CT scan and those investigations during the follow up after randomization are important secondary outcome measures. The difference in AADI, PADI, Redlund-Johnell (VT), signs of myelopathy or compression, subaxial involvement, amount of pannus tissue and signs of fusion will be registered. Failures of surgery can be recognized by screw breakage, progression of AAS or VT.

### Database

All data collected of patients participating in this trial are registered in a database under the ProMISe data management system of the Department of Medical Statistics of the LUMC. Database access is secure and limited to the trial coordinator, the trial data manager and the principal statistician. At patient enrollment into the trial, a unique study identification number is issued. The database will not contain any information directly identifying the study subject. However, to avoid errors during data collection in the follow-up of the patient, the patient's initials (first character of first name and first character of last name) will be entered as well as the gender and date of birth of the patient. The local hospital number of the patient is also part of the registration. The investigator in each participating hospital will maintain a list in which the correspondence between the true identity of the subject and its study number is documented. Follow-up data sent from each participating hospital to the central data management will only contain the study ID of the subject but not any data directly revealing the identity of the subject. It is the responsibility of each local hospital research coordinator to ensure the integrity of the correspondence between the Study ID and the true identity of the patient. The data manager will enter follow up data and verify that the date of birth of the follow up data forms is identical to the date of birth on the entry form. Discrepancies are to be solved by the local coordinator. This system ensures that only a local physician can infer the identity of any participating subject.

### Follow up

Follow up with clinical assessments and outcome measures will be assessed at baseline and after 3, 6, 12, 18 and 24 months. After two years the patient will be controlled once a year till eventually 10 years after randomization. During the follow up parameters will be registered to evaluate the quality of life, illness restrictions and neurological impairments. Direct and indirect medical costs will be calculated in each group.

Every control moment an X-ray of the cervical spine will be made (neutral/flexion/deflexion) except three months postoperatively. Prior to randomization and six months postoperatively a CT scan will be made to evaluate fusion and surgical stabilization. At fixed intervals and on clinical indication a MRI scan of the cervical spine will be performed. The clinical, neurological and radiological parameters will be registered on the follow up CRF. Data collection will take place per treatment center and will be gathered and analyzed at the LUMC in Leiden by the trial coordinator together with the statistical department and the epidemiological department of the VUMC in Amsterdam.

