**Discussion:**

Early surgery could prevent serious neurological deficits, but may have peri-operative morbidity and loss of rotation of the head and neck. The objective of this study is to identify the best timing of surgery for patients at risk for the development of neurological signs and symptoms.

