### Economic evaluation

The result of this study is based on both the short-term and long-term success of surgical intervention and prolonged conservative treatment. The economic evaluation will be performed from a societal perspective. Both health care costs and costs of production losses will be included. Health care costs will include costs of general practice care, medical specialist care, physiotherapy, hospitalisation, medication and other costs directly associated with diagnosis, treatment and rehabilitation.

There are many variable parameters influencing the total costs of the surgical fixation (surgery time, extend of surgical fixation, systems used), which makes it very difficult to calculate the real costs of the surgical procedure. Therefore, real costs of surgery will not be estimated but based on standard prices in the participating hospitals. The costs of hospital admission in the surgical group will be calculated by the days spent on the Intensive Care Unit and the surgical department. Side-effects and complications related to the treatment are recorded by the patients, the treating surgeon or rheumatologist. The costs of complications will be reflected in additional intervention, prolonged duration of ICU stay and total admission time. The costs for re-surgery in the early surgery group and surgery in the conservative group will also be estimated.

In the study MRI and CT scans will be performed in both treatment groups. The costs of these imaging techniques will be included. The costs of the CT scan will only be calculated for patients undergoing surgery, because in the normal situation, CT would only be performed if a surgical indication exists. CT scans that are only used for research purposes will not be included.

Patients will register other health care needs in a diary (including physiotherapy, visits to GP's and specialists, nursing care and medication). Each diary covers a period of 3 months. The costs of health care will be assessed using standard prices. Patient/family costs and costs of production losses will also be collected in the cost diaries.

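### No EuroQol score is scheduled between baseline and month 3, so the cost-utility analysis counts the cost of surgery but does not measure the utility loss in the weeks after it

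*Protocol article*

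**What the plan says.** The Follow up section sets the schedule: "Follow up with clinical assessments and outcome measures will be assessed at baseline and after 3, 6, 12, 18 and 24 months". It continues: "After two years the patient will be controlled once a year till eventually 10 years after randomization". Nothing is listed between baseline and month 3.

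The source of the QALYs is given under Secondary outcome parameters: "A cost-utility analysis will be performed using QALY's based on the EuroQol questionnaire". No other utility source is named.

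The Economic evaluation section costs the operation at standard prices and admission by days in intensive care and on the ward. On complications it says: "The costs of complications will be reflected in additional intervention, prolonged duration of ICU stay and total admission time". Patients also keep diaries: "Each diary covers a period of 3 months". These record care use, family costs and production losses; no utility measure is mentioned.

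The time origin of the early visits is not settled. Total follow-up is counted from randomisation, yet the imaging sentence refers to a postoperative time: "Every control moment an X-ray of the cervical spine will be made (neutral/flexion/deflexion) except three months postoperatively".

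**The concern.** The abstract's discussion says that early surgery "may have peri-operative morbidity and loss of rotation of the head and neck". The article thus expects harm around the operation, and its cost side follows that period closely. Its utility side has no measurement there. If the scores at baseline and month 3 are joined by a line, a loss that begins and ends between them leaves no trace.

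The gap is not balanced between the arms. Almost everyone allocated to early surgery is operated on. In the conservative arm surgery follows only on failure of conservative management.

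Cost-effectiveness is the second main research question. With 8% against 2% events planned over 5 years, the average QALY gain per patient is small, so a small unmeasured loss can be a material part of it.

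**Working it through.** The article states no utility loss, recovery time, waiting time to surgery or rule for joining scores, so there is no plan figure to reproduce. The planning inputs used are the 5-year event rates under Sample size/power calculation (8% and 2%, a difference of 0.06) and the visit times. The rest is assumed and shown as a range.

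**1. Loss missed when surgery is near baseline, or visits run from surgery, and recovery is complete before month 3.** Missed QALY = dip × weeks/52 × shape. The shape factor is 0.5 for a linear recovery, 1 for a full loss throughout, and 0.75 between.
- Low: 0.1 × 4/52 × 0.5 = 0.004
- Middle: 0.2 × 6/52 × 0.75 = 0.017
- High: 0.3 × 8/52 × 1 = 0.046

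**2. Yardstick: the gain over 5 years.** Gain = 0.06 × utility loss per event × 2.5 years lived on average after an event.
- Loss 0.2: 0.06 × 0.2 × 2.5 = 0.030
- Loss 0.3: 0.06 × 0.3 × 2.5 = 0.045
- Loss 0.4: 0.06 × 0.4 × 2.5 = 0.060

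In the middle case, 0.0173/0.045 = 38% of the recorded gain would be unmeasured loss. The net gain would be 0.045 − 0.0173 = 0.0277, so the recorded gain would exceed it by 0.0173/0.0277 = 62%.

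**3. Ten years.** With constant hazards (assumed), events are 1 − 0.92² = 15.4% and 1 − 0.98² = 4.0%, a difference of 0.114. At a loss of 0.3 for 5 years on average, the gain is 0.114 × 0.3 × 5 = 0.171. The middle dip is then 0.0173/0.171 = 10% of it.

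**4. Offset from the conservative arm.** Surgery there is itself an event, so at the planned rate at most 8% of that arm is operated on within 5 years. If each of those dips were also missed, the imbalance would fall by 0.08 × 0.0173 = 0.0014, from 0.0173 to 0.0159.

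**5. Dependence on the date of surgery.** Take a dip of 0.3 with linear recovery over 8 weeks, scores at weeks 0, 13 and 26 from randomisation, and straight lines between them. The true loss is 0.3 × 8/(2 × 52) = 0.0231. The week-13 score carries 13/52 = 0.25 of a year, so the recorded loss is 0.25 × the loss present at week 13.

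| Surgery at week | Loss present at week 13 | Recorded | True − recorded |
|---|---|---|---|
| 0 | 0 | 0 | +0.0231 (missed) |
| 4 | 0 | 0 | +0.0231 (missed) |
| 8 | 0.3 × 3/8 = 0.1125 | 0.0281 | −0.0050 (overstated) |
| 12 | 0.3 × 7/8 = 0.2625 | 0.0656 | −0.0425 (overstated) |

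Over a wider range (dip 0.1 to 0.5, linear recovery in 4 to 12 weeks), surgery near baseline gives 0.004 to 0.058 missed. Surgery at week 12 gives 0.011 to 0.075 overstated.

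**6. Slower recovery.** With surgery at week 0, a dip of 0.3 and recovery over 20 weeks, the true loss is 0.3 × 20/(2 × 52) = 0.0577. The loss at week 13 is 0.3 × 7/20 = 0.105, so 0.0263 is recorded and 0.0314 missed. The loss is then partly captured.

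**The case against.** A reader might infer that most operative loss has passed by month 3 and that the schedule therefore favours early surgery. The documents support neither as fact. They give no size or length of operative loss and no delay to surgery; the only remark on recovery, under Treatment, is that patients can be mobilised on the first day. The sign also depends on the visit clock. The postoperative wording for imaging leans towards visits counted from surgery, but does not settle it. This objection stands, and the direction must be conditional.

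A reader might also infer that the whole second research question is compromised. It is not. Under Cost-effectiveness and cost-utility analysis, ratios on the primary clinical effect are planned, and cost-utility ratios come in addition. The first kind uses no EuroQol score. The primary event analysis is also untouched.

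The magnitude rests on assumed values and spans a factor of about 12 (0.046/0.004). It may also be small beside sampling error. With an assumed 5-year QALY standard deviation of 0.5 to 1.0 and 125 patients per arm, the 95% half-width is 1.96 × SD × √(2/125), about 0.12 to 0.25. That is true, but a systematic error shifts the point estimate and the acceptability curve and does not average out.

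Finally, an article may leave the joining rule, an operative decrement or timing by instrument to a full protocol that is not shown. Their absence is no fault. The point rests on the schedule the article does fix, which has no utility measurement in the peri-operative weeks. If the full protocol has an earlier EuroQol, the point is answered.

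**Conclusion.** The point holds in conditional form. Followed as written, the schedule leaves the utility loss in the weeks after surgery unmeasured while its costs are counted, and the gap falls almost wholly on one arm.

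If surgery is soon after randomisation or visits run from surgery, and recovery is largely complete by 3 months, the cost-utility comparison is likely to favour early surgery by about 0.004 to 0.046 QALY per operated patient. Against an assumed 5-year gain of 0.03 to 0.06 QALY that can be material; over 10 years the share is smaller. If surgery falls shortly before a month-3 visit timed from randomisation, the error runs against early surgery. Under either clock the QALY area around the operation is unreliable.

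This is a worthwhile, cheap improvement to the cost-utility part of the second research question.

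**What to change.** - State whether the early visits run from randomisation or from surgery, and record the operation date.
- Add a one-page EuroQol to the cost diary at about weeks 2 and 6 after surgery, with matched times in the conservative arm. Repeat it after later operations in either arm where diaries are in use.
- Use these scores in the QALY area under the curve. Place every score at its actual date on one time axis from randomisation, so that the arms are not compared on different clocks.
- Add a sensitivity analysis with an assumed peri-operative decrement, over a stated range, for operations not covered by a diary. The article gives each diary's length but not how long diaries continue.

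The cost is two extra pages in a diary that patients already keep, with no extra visit. The downsides are slightly more patient burden and possibly a smaller QALY gain for early surgery. The change must come early, because scores not collected in those weeks cannot be recovered later.
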